### Data Management

The study coordinator will enter questionnaire data, as well as physical and biochemical measurements directly into Emory University’s REDCap database [30]. This database will feature validation checks to ensure data accuracy, along with skip patterns facilitated by branching logic functions. The principal investigator (ST) will constantly review the data for any errors, promptly flagging any errors for correction by the study coordinator. Upon completion of data entry and cleaning, a master copy of the data set will be generated and securely stored within the REDCap database. CGM raw data (in CSV file format per participant) will be downloaded from the DexCom Clarity software and uploaded to REDCap. Access to these datasets will be limited to the study coordinator and the principal investigator for confidentiality and data security purposes.

### Sample Size Calculation

Assuming a Cohen *d* of 0.3 to <0.7 (medium standardized effect size) [25,59] for FPG in the planned main trial, with an alpha of 5% and a power of 90%, a sample size of 15 participants per treatment group is deemed necessary for this pilot study. Factoring in a 10% loss to follow-up in each group, the total sample size was estimated to be 34 participants (17 per group).

### Statistical Analysis

#### Quantitative Research

##### Objective 1

Continuous variables will be summarized using either mean (SD) or median (IQR), depending on their distribution, which will be visually assessed through histograms. Categorical variables will be presented as counts (n) and percentages (%).

##### Objective 2

The analyses will adhere to the “intention-to-treat” principle. Between-group differences in changes in continuous variables from baseline to 8 weeks will be analyzed using mixed-effects linear regression models, while categorical variables will be assessed with log-binomial models. Skewed variables will be log-transformed prior to analysis. Fixed effects will include the study group (intervention vs control), timepoint (follow-up vs baseline), and the interaction between the study group and timepoint. Random effects will be specified for participants to account for the correlation between repeated measurements on the same individual. The *P* value for the study group-by-timepoint interaction will be used to evaluate the difference in changes between the study groups. The correlation between changes in fasting glucose levels and the indices from baseline to 8 weeks will be assessed using either Pearson or Spearman correlation coefficients, depending on the nature of the data distribution. Mixed-effects linear regression models will be used to compare CGM metrics between study groups, adjusting for baseline values. These models will also examine within-participant differences in CGM metrics between exercise and non-exercise days. Statistical significance will be considered with a 2-sided *P* value<.05 with no adjustments for the multiplicity of comparisons. All analyses will be conducted using Stata (version 18.0; StataCorp LLC).

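### The model for FPG and the other continuous clinical outcomes is a change-score comparison without baseline adjustment, which usually gives away some precision; the CGM models in the same section do adjust.

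*Protocol article*

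**What the plan says.** Under Statistical Analysis, Objective 2, the Protocol article fixes the mixed model for changes in continuous outcomes: "Fixed effects will include the study group (intervention vs control), timepoint (follow-up vs baseline), and the interaction between the study group and timepoint". It adds: "Random effects will be specified for participants to account for the correlation between repeated measurements on the same individual". The treatment effect is judged by one term, since the P "value for the study group-by-timepoint interaction will be used to evaluate the difference in changes between the study groups". Baseline therefore enters as an outcome. It is not a covariate, and the two arms' baseline means are not held equal.

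For the CGM outcomes the same section says: "Mixed-effects linear regression models will be used to compare CGM metrics between study groups, adjusting for baseline values".

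Tests are two-sided, at a P "value<.05 with no adjustments for the multiplicity of comparisons". On software it says only: "All analyses will be conducted using Stata (version 18.0; StataCorp LLC"). It names no command, no choice between maximum likelihood (ML) and restricted maximum likelihood (REML), and no degrees-of-freedom method.

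Randomization and Blinding places randomisation after the baseline assessments. Secondary Outcomes defines the clinical outcomes as between-arm differences in change from baseline to 8 weeks.

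**The concern.** Because randomisation follows the baseline measurements, any baseline difference between the arms is chance. A model that leaves the two baseline means free does not use that fact. It subtracts the whole baseline value, which amounts to assuming a slope of 1 of follow-up on baseline. Where the true slope is below 1, this adds noise and passes part of any chance imbalance into the estimate.

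At about 15 per arm, precision is scarce. The article says the trial will provide preliminary efficacy estimates and help to design a larger trial. The baseline values will be collected anyway, and the article already adjusts for baseline in the CGM analysis. FPG, the outcome named in the efficacy objective and in the sample size section, is not treated the same way.

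**Working it through.** **Inputs from the article.** The sample size section says "with an alpha of 5% and a power of 90%, a sample size of 15 participants per treatment group is deemed necessary for this pilot". Its allowance for 10% loss reproduces: 15/0.9 = 16.7, rounded up to 17 per group, 34 in total. The checks below use n = 15 per arm, and 17 where stated. The correlation rho between baseline and 8 weeks, and the SDs of FPG, are not given, so they are assumed over a range.

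**Step 1: what the planned model estimates.** In simulated complete data with 15 per arm, the group-by-timepoint coefficient from a random-intercept model equalled the difference in mean change. Its SE was identical to the change-score SE under REML, and equal to that SE times sqrt(28/30) under ML. For example, in one data set the estimate was -0.3259 with SE 0.2513 (REML and change score) and 0.2428 (ML).

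**Step 2: precision with equal variances (SD = 1).**
- Planned model: Var = 4(1 - rho)/n.
- ANCOVA, large sample: Var = 2(1 - rho²)/n. The ratio to the planned model is (1 + rho)/2.
- ANCOVA, finite sample: multiply by 1 + 1/(2n - 4) = 1 + 1/26, and use t on 27 df instead of 28.

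Worked at rho = 0.5: planned 4 × 0.5/15 = 0.133, SE 0.365. ANCOVA 2 × 0.75/15 = 0.100, times 1.038 = 0.104, SE 0.322.

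| rho (assumed) | Variance ratio, large sample | SE planned | SE ANCOVA, finite sample | 95% CI width, ANCOVA/planned | Power at 0.7 SD, planned → ANCOVA |
|---|---|---|---|---|---|
| 0.3 | 0.65 | 0.432 | 0.355 | 0.823 | 35% → 48% |
| 0.5 | 0.75 | 0.365 | 0.322 | 0.884 | 46% → 55% |
| 0.7 | 0.85 | 0.283 | 0.266 | 0.941 | 66% → 72% |
| 0.9 | 0.95 | 0.163 | 0.162 | 0.995 | 99% → 99% |
| 0.95 | 0.975 | 0.115 | 0.116 | 1.008 | not run |

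Power comes from 100,000 simulated trials per setting, with t-based tests in both analyses. All of these tests held about 5% type I error.

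**Step 3: chance imbalance.** At 17 per arm the baseline difference has an SD of sqrt(2/17) = 0.34 of an outcome SD. Subtracting baseline removes most of it. With equal variances, the part left in the estimate is (1 - rho) × 0.34: 0.17 SD at rho 0.5 and 0.10 SD at rho 0.7.

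**Step 4: FPG.** Baseline FPG must lie in 100-125 mg/dL, so the equal-variance formula does not apply directly. Simulation with that selection used an assumed between-person SD of 6-10, within-person SD of 5-6 and population mean of 100-110 mg/dL. It gives a slope of follow-up on baseline of 0.5-0.8. The ANCOVA-to-change variance ratio is about 0.88-1.01 at 15 per arm, a gain of about 0-12%.

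**Step 5: small-sample inference, conditional on the fit used.** At 15 per arm the t critical value on 28 df is 2.048.
- REML with t: type I error 5.0%.
- REML with z: 6.0%; interval width 1.960/2.048 = 0.957 of the correct width.
- ML with z: 6.9%; width 0.957 × sqrt(28/30) = 0.924.

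At 17 per arm the type I errors are 5.9% (REML, z) and 6.6% (ML, z).

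**The case against.** The strongest reply is that the clinical outcomes are defined as changes, which the interaction estimates directly. The CGM outcomes are levels during and after the intervention, for which a baseline covariate is the natural choice. This explains why the two models differ, and the contrast is not a contradiction. It does not remove the point: under randomisation the baseline-adjusted difference at 8 weeks is also the baseline-adjusted difference in change, so the definition of the outcome does not stand in the way.

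It can also be said that the gain is small for FPG, is nil for outcomes with a correlation near 0.95, and concerns secondary, preliminary outcomes. All of that stands. The article also takes the main trial's FPG effect size from cited work, so it does not say that this estimate alone will set the next sample size.

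A further fair objection concerns the remedy. Simply dropping the group term from a random-intercept model assumes equal variance at both visits, and selection on FPG breaks that assumption. In simulation with 15 per arm, that shortcut gave a type I error of 7-9% for FPG, against 5% for ANCOVA and for the planned comparison with t. Without selection it was 5.1-5.3%. The fix below allows for this.

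A reader might infer that the plan lacks a small-sample correction and that its intervals will be too narrow. The article does not support this. It names the software but neither specifies nor rules out such a correction, and an article may leave that detail to a fuller document. The same model with REML and t holds 5%. The two matters also act in opposite directions: omitting baseline adjustment usually widens intervals, while z inference narrows them.

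**Conclusion.** The point holds as a matter of efficiency. The stated model for the continuous clinical outcomes is equivalent to a change-score comparison and does not adjust for baseline. With equal variances, a baseline-adjusted analysis would have 0.65-0.85 of its large-sample variance at an assumed rho of 0.3-0.7. At 15 per arm that means a confidence interval about 18% to 6% narrower. At rho 0.9 or more there is little or no gain. For FPG the gain is about 0-12% in variance under the assumed SDs.

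A reader might take this to mean that the planned estimate is biased or the analysis invalid. It is neither: the estimate is unbiased under randomisation. The type I error of about 6% (REML) to 7% (ML) is conditional on large-sample z inference, which the article does not say is planned. As efficacy is secondary and preliminary, this is an improvement available at no cost in data and not an error that undermines the trial.

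**What to change.** In Statistical Analysis, Objective 2, state one baseline-adjusted analysis for every continuous clinical outcome. Either of these would do:
- ANCOVA on the 8-week value with the baseline value as covariate. This is the simpler choice, but it drops participants without an 8-week value.
- A longitudinal model with a common baseline mean in both arms and an unstructured covariance that allows the variance to differ between visits. This keeps participants with only a baseline value, as the planned mixed model already does, and so fits the intention-to-treat statement.

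Do not obtain the second option for FPG by merely deleting the group term from a random-intercept model.

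As an add-on, for any mixed model, state REML with Kenward-Roger or Satterthwaite degrees of freedom, unless a fuller document already does so.

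The cost is a sentence or two of text and a small change in code, with no extra data, participants or delay. P values would be slightly larger if large-sample z inference would otherwise have been used.

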One of the promising approaches is high-intensity interval training (HIIT), recognized as a time-efficient exercise option with significant benefits for metabolic health [14]. HIIT entails alternating short bursts of high-intensity exercise with periods of less active or passive recovery [15]. It is noteworthy that HIIT represents a more intensive exercise regimen compared to the current physical activity recommendations for individuals with prediabetes [10,11].

HIIT has been shown to effectively reduce hepatic insulin resistance and improve early-phase insulin secretion in individuals with type 2 diabetes [16-20], leading to significant reductions in fasting plasma glucose (FPG) levels [17,21-25]. Given that i-IFG shares these same pathophysiological defects [5-7], it is reasonable to hypothesize that HIIT could also be effective in individuals with i-IFG, as depicted in Figure 1. However, this hypothesis has yet to be tested in a randomized controlled trial (RCT). This is a critical investigation, as reducing fasting hyperglycemia is key to preventing the progression of type 2 diabetes in those with i-IFG [6,26]. To inform the design and implementation of this RCT, we propose conducting a proof-of-concept study among individuals with i-IFG, with the following objectives.

Primary objectives (feasibility and acceptability): (1) assess the feasibility of recruiting and retaining participants and executing study procedures; (2) examine the feasibility, acceptability, and appropriateness of the HIIT intervention for participants; and (3) investigate participants’ experiences, perceptions, and satisfaction with the HIIT intervention, and identify facilitators and barriers to participation.Secondary objective (preliminary efficacy): Investigate the preliminary efficacy of HIIT in reducing FPG levels and addressing the underlying pathophysiology of i-IFG.

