#### Biochemical Measures

Participants will undergo an OGTT following standard protocols [52,53]. The test will be conducted after an overnight fast of at least 10 hours, with the session scheduled between 7 and 9 AM. Venous blood samples will be collected at 0, 30, and 120 minutes after ingesting a 75-g oral glucose load dissolved in 250-300 mL of water, consumed over 5 minutes. Additionally, blood samples for insulin will be obtained at 0 and 30 minutes after glucose load ingestion. Blood samples will be processed and analyzed at the Emory Medical Laboratory (EML). EML is a fully accredited and licensed clinical laboratory, actively participating in the College of American Pathologists Laboratory Accreditation Program. Additionally, it holds Clinical Laboratory Improvement Amendments certification through the Centers for Medicare and Medicaid Services. EML is also duly licensed by the state of Georgia. Glucose levels will be assessed through enzymatic assays and insulin levels via immunoassays based on the EML protocol [53]. All these analyses will use kits provided by Beckman Coulter Inc and will be performed on a Beckman Coulter analyzer.

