##### Indices of ß Cell Function and Insulin Resistance

Table 3 provides details on the indices of ß Cell function and insulin resistance derived from glucose and insulin levels. Early-phase insulin secretion will be assessed using the insulinogenic index [54], while total ß cell function with be evaluated with the oral disposition index [55] and homeostatic model assessment of ß cell function [56]. Whole-body insulin resistance will be determined using the Matsuda index [57] and homeostatic model assessment of insulin resistance [56], while tissue-specific insulin resistance will be assessed with the hepatic insulin resistance index [58] and muscle insulin sensitivity index [58].

**Table 3 table3:** Indices of ß-cell function and insulin resistance.

ß cell function or IR^a^ and components		Indices	Formula

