**ß cell function**			
	Early-phase insulin secretion:	IGI^b^ [54]	(I_30_^c^–I_0_^d^)/(G_30_^e^–G_0_^f^)
	ß cell function	DI_O_^g^ [55]	([ I_0-30_/ G_0-30_]×[1/I_0_]) I0 in µU/l G0 in mmol/l
	ß cell function	HOMA-B^h^ [56]	(20×I_0_)/(G_0_–3.5) I0 in µU/l G0 in mmol/l

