**Insulin resistance**			
	Whole-body insulin sensitivity	Matsuda index [57]	10,000 /√((G_0_×I_0_)×(G_mean_^i^×I_mean_^j^))
	Insulin resistance	HOMA-IR^k^ [56]	(I_0_×G_0_)/22.5 I0 in µU/L G0 in mmol/l
	Hepatic insulin resistance	HIRI^l^ [58]	(G_0_–G_30_[AUC^m^]×I_0_-_30_[AUC]) G0 in mg/dl I0 in µU/ml
	Muscle insulin resistance	MISI^n^ [58]	(dG/dt^o^)/Ī^p^

^a^IR: insulin resistance.

^b^IGI: insulinogenic index.

^c^I_30_: mean insulin at 30 minutes during the oral glucose tolerance test.

^d^I_0_: mean insulin at 0 minutes during the oral glucose tolerance test.

^e^G_30_: mean glucose at 30 minutes during the oral glucose tolerance test.

^f^G_0_: mean glucose at 0 minutes during the oral glucose tolerance test.

^g^DI_O_: oral disposition index.

^h^HOMA-B: homeostatic model assessment of ß cell function.

^i^G_mean_: mean glucose during the 2-hour oral glucose tolerance test.

^j^I_mean_: mean insulin during the 2-hour oral glucose tolerance test.

^k^HOMA-IR: homeostatic model assessment of insulin resistance.

^l^HIRI: hepatic insulin resistance index.

^m^AUC: area under the curve during the first 30 minutes of the oral glucose tolerance test.

^n^MISI: muscle insulin sensitivity index.

^o^dG/dt: slope of the regression line from the peak of the plasma glucose curve to its nadir (mmol/L/min).

^p^Ī: mean insulin concentration over the 2-hour duration of the oral glucose tolerance test (pmol/L).

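### Change in fasting glucose is correlated with change in indices that themselves contain fasting glucose, so zero is the wrong null, most of all for HOMA-B

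*Protocol article*

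**What the plan says.** The secondary objective in the Introduction is to "Investigate the preliminary efficacy of HIIT in reducing FPG levels and addressing the underlying pathophysiology of i-IFG". Under Statistical Analysis, Objective 2, one analysis linking the two halves of that objective is given: "The correlation between changes in fasting glucose levels and the indices from baseline to 8 weeks will be assessed using either Pearson or Spearman" coefficients, according to distribution. The rule for all tests is "Statistical significance will be considered with a 2-sided *P* value<.05 with no adjustments for the multiplicity of comparisons".

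Table 3 lists seven indices of β-cell function and "insulin resistance derived from glucose and insulin levels". Its footnotes define G0 as "mean glucose at 0 minutes during the oral glucose tolerance test". Under Biochemical Measures there is one oral glucose tolerance test (OGTT) per assessment: "Venous blood samples will be collected at 0, 30, and 120 minutes after ingesting a 75-g oral glucose load". The 0-minute sample is the fasting sample, so it supplies both fasting plasma glucose (FPG) and G0.

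The correlation analysis does not set apart the indices that contain G0, and it gives no reference value other than zero. The limitations in the Discussion cover the use of surrogate indices and day-to-day OGTT variability, but not the shared term.

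**The concern.** When one measured quantity is an ingredient of both variables, the two are correlated by construction. A test against zero then mostly detects the formula. Here the shared quantity is the same blood sample with the same sampling error.

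This analysis would be read as evidence that the FPG response runs through the hypothesised defects. For HOMA-B and Matsuda the built-in sign is negative, and for HOMA-IR and the hepatic index it is positive. Those are the signs the hypothesis predicts: lower FPG with better β-cell function and less insulin resistance. For the insulinogenic and disposition indices the built-in sign is positive. If G0 falls and 30-minute glucose (G30) does not, the increment in the denominator widens and the index drops, so a real gain in early-phase secretion could be masked. Either way, the P value does not test what it appears to test, and the results are meant to guide a larger trial.

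**Working it through.** **Where G0 enters (Table 3).**

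| Index | Role of G0 | Built-in sign with change in FPG |
|---|---|---|
| HOMA-B | denominator, as G0 − 3.5 mmol/L | negative |
| HOMA-IR | direct multiplier | positive |
| Matsuda | direct factor, and within mean glucose | negative |
| Insulinogenic index | subtracted from G30 in the denominator | positive |
| Oral disposition index | in the 0-30 minute glucose increment | positive |
| Hepatic index | in the 0-30 minute glucose area | positive |
| Muscle index | no explicit G0 term | none directly |

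**Arithmetic that needs no assumed variability.** Take G0 = 108 mg/dL, inside the eligible range of 100-125, and let it fall by 10 with insulin unchanged.
- HOMA-B denominator: 108/18 − 3.5 = 2.50 before and 98/18 − 3.5 = 1.94 after. The ratio is 2.50/1.94 = 1.29, so HOMA-B rises 29%.
- HOMA-IR: 98/108 = 0.91, so HOMA-IR falls 9%.

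HOMA-B is the more sensitive because the eligible range is only about 2.1 to 3.4 mmol/L above the constant (100/18 − 3.5 = 2.06; 125/18 − 3.5 = 3.44).

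**Number of participants.** The protocol plans 15 per group after 10% loss: 15/0.9 = 16.7, rounded up to 17 per group, 34 in all. This reproduces the stated total. Thirty completers give a critical |r| of 0.361 at two-sided 5%. The protocol states no figure for the correlation analysis itself.

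**Simulation under no mechanism.** Changes in insulin were drawn independently of changes in glucose, the indices were computed at both visits, and their changes were correlated with change in FPG. The protocol gives no variability for either measure. Assumed: within-person FPG SD 5 mg/dL, insulin CV 0.15 or 0.25, baseline FPG about 108 mg/dL, fasting insulin about 10 µU/mL.

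| Change in FPG against change in | P<.05 at insulin CV 0.15 | P<.05 at insulin CV 0.25 |
|---|---|---|
| HOMA-B | about 92% | about 57% |
| HOMA-IR | about 28% | about 15% |
| Matsuda | about 23% | about 13% |
| Insulinogenic index, G30 independent of G0 | about 28% | about 20% |
| Insulinogenic index, G30 moving one-for-one with G0 | about 5% | about 5% |
| Fasting insulin alone (no shared term) | about 5% | about 5% |

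A correct test would give 5% in every row. Pearson and Spearman, on raw or log scales, behave alike. The insulinogenic row also depends on the assumed spread of G30.

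**Wider range.** With SD of FPG change 5 to 10 mg/dL and SD of log insulin change 0.15 to 0.35, HOMA-B gives 34% to 100%. The hepatic index gives 6% to 23% if G30 is independent of G0 and 8% to 68% if it tracks G0. The muscle index stays near 5% in the first case, but in the second gives 22% to 77% through G30. At least one of the seven correlations is significant in 58% to 100% of these trials.

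**Does CGM glucose remove the problem?** If all visit-to-visit change is noise, a glucose measure from a separate sample returns about 5% against HOMA-B. If glucose truly changes (assumed SD of true change 5 to 8 mg/dL, unrelated to insulin), HOMA-B against CGM glucose is still significant in about 22% to 79% of trials, because true G0 remains in the formula.

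**The case against.** Four points on the other side deserve weight.

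- **The stakes are limited.** This is one correlation analysis within a secondary objective. The primary outcomes are feasibility, acceptability and participants' experience. A reader might infer that the trial cannot examine mechanism at all. The protocol does not support that, because the pathophysiology indices are also compared between randomised groups, and those tests do not depend on this correlation. This point stands.
- **The artefact does not always favour the hypothesis.** A reader might take it that every coupled index would appear to confirm the mechanism. For the insulinogenic and disposition indices it runs the other way, and it disappears if G30 tracks G0 one-for-one. The largest rates belong to HOMA-B, a measure of overall β-cell function. The early-phase and hepatic measures, closest to the defects named in the Introduction, are less affected or less predictably so. This also stands.
- **The rates rest on assumed variability.** True of their size. The coupling itself follows from Table 3, and HOMA-B stays far above 5% throughout the range tried.
- **The wording could mean CGM.** The Continuous Glucose Monitoring section also speaks of fasting glucose levels. FPG is the likelier reading, and a CGM reading would remove only shared measurement error. A reader might suppose that switching to CGM cures the problem; that holds only if nobody's glucose truly changes, which is not what the trial is designed to bring about.

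**Conclusion.** The point holds in a limited form. For six of the seven indices, zero is not the correlation to expect in the absence of a mechanism, so a P value against zero is misleading. The defect is severe for HOMA-B, moderate to weak for HOMA-IR and Matsuda, and dependent on the behaviour of G30 for the rest. That G0 is shared is certain from the protocol's own formulas; the percentages depend on variability that the protocol does not give. The analysis as specified should be changed before it is run, but the trial's primary conclusions and its randomised comparisons of each index are not at risk.

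**What to change.** Amend the correlation paragraph under Objective 2:

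1. Do not correlate change in fasting glucose, whether FPG or CGM, with change in HOMA-B or HOMA-IR. Keep both as between-group outcomes.
2. Correlate change in FPG with insulin terms that contain no glucose, such as change in fasting insulin. This gives about 5% false significance under the same null.
3. For any glucose-containing index that is kept, judge the observed correlation against the one the formula alone produces. Hold each participant's glucose values fixed, permute the sets of insulin values across participants (both visits kept together), recompute the index changes, and report the resulting reference distribution beside the observed value.
4. Do not present CGM nocturnal glucose as a substitute that restores a 5% error rate.
5. State whether fasting glucose in this paragraph means FPG or a CGM measure.

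The cost is analysis wording and a few lines of code, with no new data. What is lost is the HOMA-B and HOMA-IR correlations.
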